**Figure 1: timeline development, cluster RCT and qualitative evaluation**

**2010/11**

Preparation & Randomisation PCPs (clusters)

**2011** control group

Intervention group

**2012** intervention group

Development intervention including focus group FPs (intervention group)

Focus group with FPs and PNs to evaluate success and failure factors of the intervention

Semi-structured interviews with 5 persons with cognitive impairment and their caregiver

**Figure 2: patient flow cluster RCT (goals 1-3) & diagnostic accuracy sub-study (goal 4)**

**All patients ≥ 65**

N = 7798 patients, 16 PCPs

**Patients with possible cognitive impairment according to FPs**

N = 650

**Intervention group**

8 PCPs

**1. Random sample**

N = 312

**Control group**

8 PCPs

- Outcomes in patients with a baseline diagnosis MCI or dementia on the CAMCOG and their informal caregiver

(n ~ 156)

- Patient and caregiver characteristics and outcomes (n =156)

- CAMCOG (n =156)

- CAMCOG (n = 156)

- Quality of care indicators, diagnostic (N=156) & management indicators in patients with dementia (n ~ 50)

**Measurement**

- Patient and caregiver characteristics and outcomes (n =156)

- CAMCOG (n =156)

- Outcomes in patients with a baseline diagnosis MCI or dementia on the CAMCOG and their informal caregiver

(n ~ 156)

**T0 Baseline**

**6 months**

**12 months**

**18 months**

**24 months**

**12 months**

- CAMCOG (n = 156)

- Quality of care indicators, diagnostic (N=156) & management indicators in patients with dementia (n ~ 50)

**2. Random sample, stratified on age, gender, GP (to mirror sample 1)** N=100

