# 2. OBJECTIVES

Our primary objective is to estimate whether a multifaceted intervention including collaboration of FPs and trained practice nurses in the diagnosis of mild cognitive impairment (MCI) and dementia and in subsequent management improve the quality of the diagnostic process and the quality of care.

Secondary objectives are to investigate:

a) Whether this intervention improves the general wellbeing of dementia patients and their informal caregivers;

b) The accuracy of the FPs’ cross-sectional classification of the cognitive status of all patients ≥ 65 years and c) whether the intervention is cost-effective

d) Success and failure factors of this intervention.

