# 3. STUDY DESIGN

To estimate the effects of the intervention on quality of the diagnostic process, quality of care and on patient and caregiver wellbeing, a stepped wedged cluster RCT design over 24 months will be used. Stepped wedged means that all practices eventually apply the intervention but the starting point per practice is randomised in early and late starters (>12 months). This design is also used for the cost-effectiveness analysis (Figure 1).

To study the accuracy of the FPs cognitive classification we will use a classical Diagnostic Test Accuracy Design. The cross sectional classification of the FP is compared to a reference standard diagnosis. Both patients initially classified with (N~312) and without (N~100) cognitive impairment according to the FPs are recruited. Equal numbers of patients will be randomly sampled per PCP.

For the evaluation of the implementation process, semi structured interviews and focus groups are held with FPs, practice nurses, key representatives of local dementia services as well as with couples of demented persons and their informal caregivers.

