## Exclusion criteria

1. Patients allready diagnosed with dementia.
2. Patient or (if present) caregiver terminally ill.
3. Permanent admission of the patient to a nursing home expected within 6 months.
4. The patient is not/no longer sufficiently capable of understanding spoken language or expressing him- or herself.

Diagnostic Test Accuracy Study: In order to also get information about the negative predictive value of the FPs cognitive classification, an additonal sample will be drawn of patients FPs classified as ‘no signs of cognitive impairment’ (Figure 2).

The study population for the process evaluation of succes and failure factors of the intervention consists of FPs and practice nurses in the intervention group. In addition, a random selection of patients and caregivers in the intervention group is invited to participate in a semi-structured interview.

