We based this calculation on a previous study on an educational intervention to improve the number of dementia diagnoses in primary care(Perry et al. ). Perry et al. conducted a cluster RCT design in which they asked 105 FPs to select 5 patients in whom they suspected cognitive impairment. FPs collaborated with a practice nurse in diagnosing dementia. In the intervention group, dementia was diagnosed in 49.1% (130 new diagnoses in 265 patients at risk) of these patients, in the control group in 14.8% (20 new diagnoses in 135 patients at risk) of these patients, after one year. Using the probabilities of Perry et al. and assuming a power of 90%, 20% loss to follow-up and adding 10% for clustering within practices resulted in a desired sample of 55 patients per arm.

Diagnostic accuracy of FPs’ classification at baseline

The diagnostyic accuracy is expressed in the positive and negative predictive value of the FPs at baseline. When we include 312 patients, initially classified by the FPs as cognitive impaired as well as and100 patients initially classified with no cognitive impairment, we reach a confidence interval of 17.9% around the point estimate, assuming a prior positive predictive value of 30%.

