# STATISTICAL ANALYSIS

## Descriptive statistics

The diagnostic accuracy of the FPs will be described (goal 4).

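### The 100 unsuspected patients are drawn to mirror the suspected ones, so a crude negative predictive value would not describe the FPs' no-signs list or all patients aged 65 or over

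*Protocol*

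**What the plan says.** - **Target.** Protocol section 2, secondary objective (b), is the accuracy of the FPs' "cross-sectional classification of the cognitive status of all patients ≥ 65 years".
- **Measure.** Section 4.4 says that accuracy is "expressed in the positive and negative predictive value of the FPs at baseline".
- **Purpose of the second sample.** Under section 4.3 the extra patients are drawn "In order to also get information about the negative predictive value of the FPs cognitive classification", from those the FPs placed in the no-signs class.
- **How they are drawn.** Figure 2 (section 7.3) specifies "Random sample, stratified on age, gender, GP (to mirror sample 1", with N=100 from 7148. Section 3 says only "Equal numbers of patients will be randomly sampled per PCP" and mentions neither age nor gender.
- **Precision.** Section 4.4 takes 312 suspected patients "and100 patients initially classified with no cognitive impairment", preceded by a linking phrase, and gives a confidence interval of 17.9% at an assumed positive predictive value (PPV) of 30%.
- **Analysis.** Section 9.1: "The diagnostic accuracy of the FPs will be described (goal 4". No weighting or standardisation is mentioned.
- **Counts.** Figure 2 starts from "N = 7798 patients, 16 PCPs" and splits them into 650 suspected and 7148 unsuspected. Section 5.1 gives the FPs four classes, including *probable dementia* and *not in sight*.

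**The concern.** A predictive value depends on how common the condition is in the group sampled. If unsuspected patients are selected to the age, gender and practice mix of suspected patients, the proportion unimpaired among them is the NPV for that mix. It equals the NPV of the whole no-signs list only if the two mixes are the same, or if missed impairment does not vary with age, gender or practice.

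Mirroring suits a comparison of suspected with unsuspected patients at equal age. Here the stated purpose is an NPV bearing on all patients aged 65 or over. What is at stake is research question 4: how often an FP's judgement of no impairment can be relied on across the elderly list. If suspected patients are the older group, the crude figure would overstate how many patients FPs miss.

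**Working it through.** **1. The plan's own precision figure.** Inputs from section 4.4: p = 0.30, n = 312 or 100. The 95% level is an assumption, since none is stated for this interval. Full Wald width = 2 × 1.96 × √(p(1−p)/n).

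- n = 100: 2 × 1.96 × √(0.21/100) = 17.96%, which agrees with 17.9% up to truncation.
- n = 312: 2 × 1.96 × √(0.21/312) = 10.17%.

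The stated figure is thus a simple unweighted interval on 100 patients, although the text ties it to the PPV, whose denominator is 312.

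**2. Size of the NPV shift.** NPV = 1 − Σ(age share × proportion impaired among unsuspected patients). The documents give no ages and no impairment rates by age, so every input here is an assumption.

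- Age mix of all unsuspected patients (65–74 / 75–84 / 85+): 55/35/10%.
- Mirrored mix: moderately older 35/45/20%, or much older 15/50/35%.
- Missed impairment by age band: low 3/8/15%, middle 5/15/30%, high 10/25/45%.

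Worked example (middle rates, moderately older): whole list 1 − (0.0275 + 0.0525 + 0.0300) = 89.0%; mirrored 1 − (0.0175 + 0.0675 + 0.0600) = 85.5%; difference −3.5 points.

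| Mirrored mix | Rates | NPV, whole list | NPV, mirrored, crude | Difference (points) |
|---|---|---|---|---|
| Moderately older | low | 94.05% | 92.35% | −1.7 |
| Moderately older | middle | 89.0% | 85.5% | −3.5 |
| Moderately older | high | 81.25% | 76.25% | −5.0 |
| Much older | low | 94.05% | 90.3% | −3.75 |
| Much older | middle | 89.0% | 81.25% | −7.75 |
| Much older | high | 81.25% | 70.25% | −11.0 |
| Same mix | any | – | – | 0 |
| Any mix | equal at all ages | – | – | 0 |

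**3. Cost of weighting back.** Weighting design effect = Σ(whole-list share² / mirrored share).

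- Moderately older: 0.55²/0.35 + 0.35²/0.45 + 0.10²/0.20 = 1.19; √1.19 = 1.09.
- Much older: 0.55²/0.15 + 0.35²/0.50 + 0.10²/0.35 = 2.29; √2.29 = 1.51.

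The interval is therefore roughly 1.1 to 1.5 times as wide as for a simple random sample of 100, before practice clustering. These factors hold when missed impairment is equal across age bands. With the age-graded rates above, the stratified variance Σ share² × rate × (1 − rate)/(100 × mirrored share) gives about 0.94 to 1.24 times the simple-random-sample width, so 1.5 is cautious.

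**4. Practice fractions.** Equal numbers per practice means about 312/16 = 19.5 suspected and 100/16 = 6.25 unsuspected patients each. Unless practices have similar numbers in each class, sampling fractions differ by practice. This affects the PPV as well, whereas the mirroring does not.

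**5. Counts.** 650 + 7148 = 7798, the full total in Figure 2. That leaves no separate place for *probable dementia* or *not in sight*.

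**The case against.** **Stratified sampling followed by weighting is legitimate, and an analysis plan that is not shown may contain the weighting.** This is the strongest counter-argument. Section 9.1 does not commit to a crude NPV, and an interval used for planning does not define an estimator. It stands to this extent: the sample itself need not change. But the sampling scheme is fixed in the protocol and does not fit the stated target, and the protocol's precision figure and its one analysis sentence both read as unweighted. That is a mismatch within the protocol, beyond detail left for later.

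**The direction is inferred.** A reader might conclude that the NPV is certain to be too low. The documents do not show this, because they give neither ages nor missed-impairment rates by age. Matching on gender and GP adds a shift of unknown direction. The age-related shift can also be no larger than sampling error: at an NPV of 90% with n = 100, the 95% half-width is about 5.9 points (1.96 × √(0.09/100)).

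**Sensitivity and specificity.** A reader might infer that these would be distorted by pooling the 312 and the 100. Section 4.4 names only the two predictive values and no such pooling is planned, so this is not part of the point.

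**The frame.** A reader might infer that the 7148 must include patients never classed as no-signs. That does not follow: the 7798 may omit the other classes, or the 650 may include probable dementia. Section 4.3 already restricts the draw to the no-signs class. Only the counts need clarifying.

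**Conclusion.** The concern holds in a limited form. Followed as written, Figure 2, the unweighted precision figure and section 9.1 together give an NPV for the suspected patients' age, gender and practice mix. Objective (b) asks about all patients aged 65 or over, and the NPV it needs is that of the no-signs list.

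The crude NPV is likely too low if suspected patients are older and missed impairment rises with age. Under the assumed mixes and rates the shortfall is about 2 to 11 points, and it is zero under equal mixes or age-independent rates. The documents cannot narrow that range.

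If section 3 rather than Figure 2 governs the draw, with no matching on age or gender, only the unequal practice fractions remain. The point affects a secondary, cross-sectional objective and leaves the trial's primary outcome untouched.

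**What to change.** 1. Keep the sample, but state in section 9.1 that the NPV will be standardised to the no-signs list. Weight on coarse age bands and sex, or rake to the age, sex and practice margins, and give practice-clustered intervals. Full cross-classification is unworkable: three age bands × two sexes × 16 practices = 96 cells for 100 patients.
2. Where equal numbers per practice give unequal sampling fractions, weight the PPV by practice.
3. Restate the NPV precision with the weighting design effect, and say which denominator the 17.9% refers to.
4. Reconcile section 3 with Figure 2 on how the 100 are drawn.
5. Show in Figure 2 where *probable dementia* and *not in sight* patients are counted.

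The cost is mainly wording. The age, gender and practice data are already needed to draw the sample. The real downside is precision: a design effect of about 1.2 to 2.3 under the assumed mixes, or an interval roughly 1.1 to 1.5 times as wide, before clustering.

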**Patients without cognitive impairment according to FPs**

N = 7148

- CAMCOG

Demografie

ADL, Chr zkt, contact freq huisarts

(n =100)

## Withdrawal of individual subjects

Study participants can end their participation at any point in time without having to give any reason for this. This will not in any way affect the care they receive.

## Replacement of individual subjects after withdrawal

Participants withdrawing from the study will not be replaced; we will include a closed cohort.

## Follow-up of subjects withdrawn from treatment

We will try to find out what the reason of withdrawal was by offering subjects who have withdrawn a short telephone interview. If they do not whish to collaborate in this, this will of course be respected.

## Premature termination of the study

< *Please describe the criteria for terminating the study prematurely and the procedures in case the study will be terminated prematurely.*>

# SAFETY REPORTING

## Section 10 WMO event

In accordance to section 10, subsection 1, of the WMO, the investigator will inform the subjects and the reviewing accredited METC if anything occurs, on the basis of which it appears that the disadvantages of participation may be significantly greater than was foreseen in the research proposal. The study will be suspended pending further review by the accredited METC, except insofar as suspension would jeopardise the subjects’ health. The investigator will take care that all subjects are kept informed.

## Adverse and serious adverse events

< *Please describe the procedures for handling the adverse and serious adverse events. If certain SAEs do not require immediate reporting, please specify*.>

Adverse events are defined as any undesirable experience occurring to a subject during a clinical trial, whether or not considered related to the investigational drug. All adverse events reported spontaneously by the subject or observed by the investiga­tor or his staff will be recorded.

A serious adverse event is any untoward medical occurrence or effect that at any dose results in death;

- is life threatening (at the time of the event);
- requires hospitalisation or prolongation of existing inpatients’ hospitalisation;
- results in persistent or significant disability or incapacity;
- is a congenital anomaly or birth defect;
- is a new event of the trial likely to affect the safety of the subjects, such as an unexpected outcome of an adverse reaction, lack of efficacy of an IMP used for the treatment of a life threatening disease, major safety finding from a newly completed animal study, etc.

All SAEs will be reported to the accredited METC that approved the protocol, according to the requirements of that METC.

### Suspected unexpected serious adverse reactions (SUSAR)

<C*hapters 8.2.1 and 8.2.2 are only applicable for studies with an investigational medicinal product.*

<*Please describe also the method of breaking the code for SUSAR reporting*.>

Adverse reactions are all untoward and unintended responses to an investigational product related to any dose administered.

Unexpected adverse reactions are adverse reactions, of which the nature, or severity, is not consistent with the applicable product information (e.g. Investigator’s Brochure for an unapproved IMP or Summary of Product Characteristics (SPC) for an authorised medicinal product).

The sponsor will report expedited the following SUSARs to the METC:

- SUSARs that have arisen in the clinical trial that was assessed by the METC;
- SUSARs that have arisen in other clinical trial of the same sponsor and with the same medicinal product, and that could have consequences for the safety of the subjects involved in the clinical trial that was assessed by the METC.

The remaining SUSARs are recorded in an overview list (line-listing) that will be submitted once every half year to the METC. This line-listing provides an overview of all SUSARs from the study medicine, accompanied by a brief report highlighting the main points of concern.

The sponsor will report expedited all SUSARs to the competent authority, the Medicine Evaluation Board and the competent authorities in other Member States.

< *SUSARs that are already reported to the EMEA Eudravigilance database do not have to be once again reported to the competent authority and the MEB because they have direct access to the Eudravigilance database.*>

The expedited reporting will occur not later than 15 days after the sponsor has first knowledge of the adverse reactions. For fatal or life threatening cases the term will be maximal 7 days for a preliminary report with another 8 days for completion of the report.

### Annual safety report

< *The annual safety report may be combined with the annual progress report (see chapter 12.3)*.>

In addition to the expedited reporting of SUSARs, the sponsor will submit, once a year throughout the clinical trial, a safety report to the accredited METC, competent authority, Medicine Evaluation Board and competent authorities of the concerned Member States.

This safety report consists of:

- a list of all suspected (unexpected or expected) serious adverse reactions, along with an aggregated summary table of all reported serious adverse reactions, ordered by organ system, per study;
- a report concerning the safety of the subjects, consisting of a complete safety analysis and an evaluation of the balance between the efficacy and the harmfulness of the medicine under investigation.

## Follow-up of adverse events

All adverse events will be followed until they have abated, or until a stable situation has been reached. Depending on the event, follow up may require additional tests or medical procedures as indicated, and/or referral to the general physician or a medical specialist.

## Data Safety Monitoring Board (DSMB)

<*In case a DSMB is established to perform ongoing safety surveillance and to perform interim analyses on the safety data, this committee should be an independent committee. The composition of DSMB should be described and it should be clear that each member has no conflict of interest with the sponsor or company of the study*.>

<*Criteria on which the DSMB may decide to terminate the trial prematurely should be clearly defined before the trial has started.*>

# STATISTICAL ANALYSIS

## Descriptive statistics

The diagnostic accuracy of the FPs will be described (goal 4).

## Univariate analysis

Not applicable

## Multivariate analysis

We will do multilevel multivariate analysis to compare the two care conditions controlling for baseline imbalance and clustering effects within practices on number of incident diagnoses (goal 1), quality of care (goal 2) patient and caregiver outcomes (goal 3). Effect modification will be explored on principal characteristics (age, gender, severity dementia and type of caregiver). A post hoc analysis on main outcomes will be done on patients who score under critical cut off on CAMCOG at baseline (<86).

In addition, an economic evaluation is performed from societal perspective comparing the effects of goals 1 to 3 and costs in the two conditions. To compare costs between the two groups, confidence intervals for the differences in mean costs are calculated using bias-corrected and accelerated bootstrapping with 5000 replications. For the cost-effectiveness analysis the difference in total costs between the intervention and usual care group are compared with the difference in main clinical outcomes.

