### Secondary study parameters/endpoints (if applicable)

Patient and caregiver wellbeing and cost-effectiveness:

**Appendix 3** provides an overview of caregiver and patient outcomes and potential effect modifiers measured. There is no information on cost-effectiveness of this type of interventions. Therefore we will also measure health care utilisation of both the patient and the caregiver, including time till institutionalisation of the person with dementia. In order to assess a long term effect we will follow patients and their informal caregivers for the period of three years.

Diagnostic accuracy study: the FPs cognitive classifications ‘possible cognitive impairment/dementia’ and ‘no signs of cognitive impairment’ are compared to the CAMCOG diagnosis on the presence or absence of dementia or MCI.

Feasibility of the intervention:

The level of implementation will be measured. For this the PN will record all her activities in a diary; additionally medical records are used.

Success and failure factors of the intervention at different levels will be derived from (2) focus groups with FPs and PNs. Additionally semi-structured interviews will be conducted with 5 persons with dementia and their informal caregiver, in order to also include the patient perspective.

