### Other study parameters (if applicable)

## Randomisation, blinding and treatment allocation

We will use prognostic stratification before randomisation. Each primary care practice will be stratified based on the two most important potential effect modifiers. Based on previous research of Perry et al. these are a) whether FPs collaborate with a practice nurse and b) the percentage of elderly patients within practices.

**Figure 2** provides an overview of the patient flow of the cluster RCT.

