## Study procedures

Subjects will not undergo any new or experimental treatment in the course of this study. Their providers will be trained to deliver care (both the process of diagnosis, disclosure and psychoeducation and the process of follow-up care management and support) in closer concordance with current guidelines. Care will become more structured both at the level of the PCP and within the region. For the subjects this will presumably result in an earlier and more thorough assessment of their care needs and earlier intervention or referral. No subjects will be withheld from treatment. We aim to introduce the intervention also in the control group. Because of feasibility the intervention will be introduced in this group one year later.

*Eligibility*

The researchers will assess eligibility of all patients for the study that were diagnosed with dementia. Before approaching potential participants, FPs will go through the list of potential participants to see whether there are any other contraindications, besides the predefined exclusion criteria, to study participation of these persons.

*Recruitment*

Subjects will be informed about the study by means of an invitational letter from their FP and an information leaflet with detailed information about the study: aim of the study, what participation means for participants, freedom to not participate or to end participation at any time without having to give a reason, etc. Subjects are encouraged to discuss the matter with friends or relatives or with their FP. Some subjects may not want to be contacted about the study. They can communicate this by returning a form by post: on this form subjects can indicate that they are not interested to participate in the study and that they do not want to be contacted. A return envelope is provided. (letter and information leaflet are added to this protocol as separate documents)

If subjects do not object, they are contacted by telephone by one of the researchers. Additional clarification about the study is provided, if needed. Subjects are asked whether they are interested to participate in the study. If this is so, an appointment will be made for obtaining informed consent and for the baseline interview.

*Informed consent*

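### The analysis section contrasts care conditions in a 24-month crossover design without a visit term or a stated time window, so secondary and cost results that use data after month 12 could be confounded with time

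*Protocol*

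**What the plan says.** **Design.** Protocol section 3 states that, to estimate effects on quality of care and on patient and caregiver wellbeing, "a stepped wedged cluster RCT design over 24 months will be used". What is randomised is the start date: "the starting point per practice is randomised in early and late starters (>12 months". The same section applies this design to the cost-effectiveness analysis. Section 7.3 says of the control practices: "Because of feasibility the intervention will be introduced in this group one year later". Figure 1 shows the same switch.

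**Analysis.** Section 9.3 will "compare the two care conditions controlling for baseline imbalance and clustering effects within practices" for incident diagnoses, quality of care, and patient and caregiver outcomes. On subgroups it says: "Effect modification will be explored on principal characteristics (age, gender, severity dementia and type of caregiver". Cost differences get confidence intervals "using bias-corrected and accelerated bootstrapping with 5000 replications"; the resampling unit is not given.

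**Randomisation.** Section 7.2 says: "Each primary care practice will be stratified based on the two most important potential effect modifiers". These are collaboration with a practice nurse and the percentage of elderly patients.

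**Time horizons.**
- *12 months:* the quality-indicator comparison (section 4.4, Appendix 2), the diagnosis count, and the wellbeing parameters in the Summary.
- *24 months:* section 3 and Appendix 3, whose last visit is T4.
- *Three years:* the secondary-endpoint text in section 7.1, which plans, in order to assess a long-term effect, that "we will follow patients and their informal caregivers for the period of three years".

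**The concern.** In a one-step wedge, care condition and randomised arm are the same thing only until the controls cross over. After that every practice gives the intervention. All usual-care observations then come from the first year, and all observations at 18 and 24 months are treated, in a closed cohort. A contrast of conditions that pools these visits without a time term compares early visits with late ones as well as usual care with intervention. Any change that would have happened anyway is partly credited to, or charged against, the intervention.

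Section 3 makes the 24-month design the basis for estimation. Section 9.3 makes condition the contrast and lists what is controlled. Nothing in the protocol confines the contrast to the first year for costs or for the outcomes that Appendix 3 schedules at 18 and 24 months. The biased analysis is therefore permitted, though not prescribed.

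Two smaller matters sit in the same paragraph. The model adjusts for an unspecified baseline imbalance and does not name the two factors used to stratify randomisation. The cost bootstrap is described without the allowance for practices that the model has.

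**Working it through.** The plan states no figure that tests this point, so there is none to reproduce first.

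**1. Which outcomes are exposed.** At 12 months both arms are measured at the same time and the late arm is still untreated, so period bias is zero. That covers the quality indicators (measured at baseline and 12 months only), the diagnosis count, and wellbeing as set in the Summary. What remains is burden, quality of life and care use at 18 and 24 months, GHQ-12 at 24 months, and costs, if these enter a comparison by condition.

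**2. Share of natural change absorbed.** Take follow-up at 12 and 24 months. The early arm is treated at both; the late arm is untreated, then treated. Let the outcome change by δ per year in everyone, with no true effect. With correlation ρ between the two visits' practice means, generalised least squares with an intercept and a condition term gives

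bias / δ = 2(1 + ρ) / (3 + ρ).

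This runs from 0.67 at ρ = 0 through 0.86 at 0.5 to 0.97 at 0.9.

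For practice means of m patients, ICC c and within-person correlation r,

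ρ = [c + (r − c)/m] / [c + (1 − c)/m].

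The trial has 312 patients in 16 practices, or 19.5 each; less 20% loss this is 15.6, taken as m = 16. The values of c and r are assumed. With c = 0.02 the denominator is 0.02 + 0.98/16 = 0.08125.

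| r | numerator | ρ | bias / δ |
|---|---|---|---|
| 0.3 | 0.0375 | 0.46 | 0.84 |
| 0.5 | 0.0500 | 0.62 | 0.89 |
| 0.7 | 0.0625 | 0.77 | 0.94 |

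With visits at 6, 12, 18 and 24 months the same calculation gives 0.90–0.97. Section 4.4 expects about half the patients to have a caregiver; with m = 8 the 12- and 24-month figures are 0.82–0.93. With a fixed visit effect the bias is zero in every case.

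**3. On the GHQ-12 scale.** The planning difference in section 4.4 is 2.2 points. The protocol gives no natural yearly change, so a range is assumed:
- 0.5 point a year: at least 0.84 × 0.5 = 0.42, or 19% of 2.2
- 1 point a year: 0.89 × 1 = 0.89, or 40%
- 2 points a year: up to 0.94 × 2 = 1.88, or 85%

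The sign follows the sign of the drift.

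**4. What a visit term leaves.** In the two-visit layout the effect is then identified only by the year-one contrast. Its variance is (1 − ρ²) times that of the plain 12-month comparison (0.75 at ρ = 0.5). Year two sharpens the estimate but adds no usual-care control.

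**5. Strata.** Section 4.4 assumes a between-practice SD of 3 and a within-practice SD of 35. With 19.5 patients per practice the variance of a practice mean is 9 + 1225/19.5 = 71.8. If the strata explained all the between-practice variance it would be 62.8. The SE ratio is √(71.8/62.8) = 1.07 at most.

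**6. Cost bootstrap.** If patients were resampled, the design effect ignored is 1 + (15.6 − 1) × ICC, with the ICC assumed.

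| ICC | design effect | interval too narrow by | coverage of a 95% interval |
|---|---|---|---|
| 0.01 | 1.146 | 1 − 1/√1.146 = 7% | 93% |
| 0.05 | 1.73 | 1 − 1/√1.73 = 24% | 86% |

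**The case against.** The strongest reply is that the comparisons that matter most all precede the crossover, and that for GHQ-12 section 4.4 also expects results at 12 months. This stands. A reader might infer that the trial's main result is biased; the protocol does not support that.

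Second, section 9.3 nowhere says that 18- and 24-month data are pooled by condition. Its cost sentences speak of two groups, which fits a comparison of randomised arms, and a visit-by-visit comparison of arms is not confounded with time. Model terms are often left to an SAP. This makes the bias conditional. It does not remove the point, because the protocol itself fixes a 24-month crossover design and a contrast by condition, and it gives three different horizons.

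Third, a reader might conclude that the bias runs against the intervention because dementia is progressive. GHQ-12 measures caregivers, patients already diagnosed with dementia are excluded, and no natural rate or direction is given. The direction is unknown.

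Fourth, it is tempting to say that effects after 12 months have no control at all. A randomised contrast of early with late start remains; what is lost is the contrast with usual care.

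Fifth, Appendix 3 lists practice-nurse presence and the percentage aged 65 or over among potential effect modifiers and confounders, and adjusting for baseline imbalance may be meant to cover them. So the strata have not been forgotten, and no selection rule is stated that would distort error rates. Likewise, patient-level resampling is one reading of a sentence that names no unit.

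**Conclusion.** The point holds in conditional form and should be fixed. Section 9.3 does not say how data after the crossover enter, although section 3 makes the 24-month design the basis for estimating wellbeing effects and cost-effectiveness. If those data were analysed by care condition without a visit term, the estimate would carry most of a year's natural change. The sizes rest on an assumed within-person correlation, ICC and yearly drift; none is in the protocol.

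The conflict between 12 months, 24 months and three years needs no assumption: the three-year aim fits neither section 3 nor the last visit in Appendix 3. The strata adjustment is a small gain. The bootstrap unit is an ambiguity whose cost would be modest to material, depending on the ICC. The quality-indicator and diagnosis comparisons at 12 months are not threatened.

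**What to change.** In section 9.3:

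1. State that the effect for every outcome, and for cost-effectiveness, is the between-arm difference over the randomised 0–12 month period.
2. Require a fixed visit or period effect in any model that uses data after month 12, and label those results early versus late start.
3. Reconcile 12 months, 24 months and three years across the Summary, section 3, section 7.1 and Appendix 3. Call anything beyond 12 months descriptive or early versus late start.
4. Replace the unspecified baseline imbalance by the two stratification factors and the baseline value of the outcome. Optionally name those two factors in the effect-modification sentence too.
5. State that the cost bootstrap resamples whole practices.

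No new data are needed, since both stratification factors are already collected. The price is wording, a little more analysis work, a few degrees of freedom among 16 practices, and wider cost intervals if patients would otherwise have been resampled.
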